### Intervention and control condition

Participating schools will be randomly assigned using a toss of a coin to the control or intervention condition. Schools will be paired on SES ranking, location and size, with one of the pair being randomly allocated as a control school and the other as an intervention school. Apart from the 3 testing sessions, the control school will follow the normal curriculum.

Teachers from the Intervention schools will be provided with comprehensive training in the *Animal Fun *Program either at their school or at Curtin University with presentations from the lead investigators. Information will be provided not only on the actual implementation of the *Animal Fun *activities but on the background and rationale for the project. The implementation of the program will be monitored with regular visits from the Research Coordinator to provide support to teachers and to obtain their feedback regarding children's enthusiasm for the activities, appropriateness of activity level of difficulty ratings and to discuss any issues or obstacles to including the program in their daily curriculum.

Teachers will also be asked to complete a weekly dosage report indicating which of the *Animal Fun *activities were implemented into the curriculum for that week and an estimate of the total time spent on *Animal Fun *for the same time period.

#### Animal Fun Program

The *Animal Fun *program was developed as a Pre-Primary program to promote motor and social development. This is a universal program for all children within the class. By including all children it reduces the stigma associated with being placed into a 'special' program. In order to accommodate the needs of all children, the program was developed to provide considerable flexibility. It does not give set lessons but provides information on the difficulty level of each activity. The rate at which the level of difficulty is increased is left to the discretion of the teachers who may choose to accelerate children as required. Teachers may also choose to group children according to different skill levels and provide the more advanced children with more challenging skills.

The *Animal Fun *program, consists of the following modules:

Module 1: Body Management (Static balance, Dynamic balance, Climbing)

Module 2: Locomotion (Walking, Jumping, Hopping, Skipping)

Module 3: Object Control (Throwing, Catching, Kicking)

Module 4: Body Sequencing (Trunk, Limbs)

Module 5: Body and Kinaesthetic Management: Trunk and Upper Limb (Eye hand coordination, Visual-kinaesthetic)

Module 6: Fine Motor Planning

Module 7: Tool Control (Pre-scissor/scissor skills, Paint brush use, Drawing/pre-writing skills)

Module 8: Hand Skills (Individual finger strength, Grip strength, Pincer grip)

Module 9: Social/Emotional Development (Laughter, Identifying and labelling feelings, Breathing, Relaxation)

The program includes 30 minutes each day for 4 days/week, usually with an outdoor session of 15 minutes and an indoor session of 15 minutes per day (but allowing flexibility depending on weather etc). Each session focuses on the development of different skills that are linked in with local education system curriculum requirements. Teachers are encouraged to increase the difficulty level as the school term progresses. The program was designed to run for an entire semester (half a year) but should be implemented for at least 10 weeks.

### Outcome Measures

#### Motor ability

Two assessment tools for motor ability will be used as these tools measure different aspects of motor performance. For example, the Bruininks-Oseretsky Test for Motor Proficiency (BOT-2) provides a measure of muscle strength and bi-lateral coordination in addition to the MABC components of manual dexterity, ball skills and balance.

The BOT-2 [53] is the most widely used motor proficiency test, and is designed to assess important aspects of motor development including both gross motor and fine motor components. It is appropriate for examinees from 4-21 years of age and can be used with normal and developmentally disabled children. The test is standardized and norm referenced. In order to minimize participation burden, the Short Form of the test will be used which includes 14 test activities. The average test-retest reliability for the complete battery is 0.87.

The Movement Assessment Battery for Children-2 (MABC-2)[54] is suitable for children aged 3 to 17 years and comprises 8 tasks, three measuring manual dexterity, 3 measuring aiming and catching and 2 measuring balance. Age norms are used to determine an overall standard score and separate standard scores for each of the 3 sub-tests. In addition to the total score a set of qualitative observations allows the examiner to record the child's performance characteristics during the testing. Minimum value of the test-retest reliability of the original MABC is 0.75 and the inter-tester reliability is 0.70. The MABC has been found to correlate well with other motor skill tests [55].

#### Psychosocial Variables

The Social Skills Rating Scale (SSRS)[56] is a standardised measure of social skills appropriate for children aged between 3 and 18 years old. It has a parent (SSRS-P) and a teacher (SSRS-T) version. Both will be used in the current project. The SSRS-P Elementary Level is a 55 item questionnaire consisting of a social skills scale (cooperation, assertion, responsibility and self control) and a problem behaviour scale (externalizing, internalizing and hyperactivity) [56]. The SSRS-T Elementary Level is a 57 item questionnaire consisting of the same two scales, although it does not include the responsibility subscale. The parents and teachers rate the frequency and importance of the child's social skills/behaviours along a three point Likert scale "(i.e., Never, Sometimes, Very Often)" [57] (p.202). The SSRS-T also rates a child's academic competence using a five point Likert scale (i.e. Lowest 10%, Next Lowest 20%, Middle 40%, Next Highest 20%, Highest 10%). The internal coefficients were 0.90 for self-control, 0.88 for interpersonal skills and 0.84 for verbal assertions [58].

The Strengths and Difficulties Questionnaire (SDQ) [59] is a brief behavioural screening questionnaire designed for children aged 4 to 16 years that contains 25 items covering five clinical scales: hyperactivity/inattention, emotional symptoms, conduct problems, peer relationship problems and prosocial behaviour. Summing all the scores from the scales except the prosocial scale generates a total difficulties score. Internal consistency coefficients (Cronbach's α) ranged from .85 for total difficulties to .64 for peer problems. Goodman reported 2-week test- retest reliability of .96 for the TDS. The SDQ correlates highly with the other similar questionnaires although it was considered more sensitive in detecting inattention and hyperactivity and equally effective in detecting internalizing and externalizing problems, and has adequate discriminant and predictive validity [59].

The Pictorial Scale of Perceived Competence and Acceptance (PSPCSA) [60] is a self report measure of perceived competence (physical and cognitive) and perceived social acceptance (peer and maternal) designed for use on children aged 4 - 7 years. This measure was developed as a downward extension of the Perceived Competence Scale for Children [61]. The tool was standardised on a homogeneous population of 191 young children who were mostly Caucasian (96%) and from middle class backgrounds. The pictorial scale consists of 24 items presented in gender specific booklets based around the four subscales of cognitive competence, physical competence, peer acceptance, and maternal acceptance. The reliability and the validity of the scale have been found to be acceptable and stable over 3 years [62]. The internal consistency reliability of the scale was found to be .89 for children with a mean age of 4.45 years based on a population of 90 preschoolers [60]. The test-retest reliability of the PSPCSA was found to be moderate to good on a population of 24 young children with language delays over an 10 - 22 day period (r = .62 - .81) [63].

#### Anthropometric Variables

In addition to the above measures, each child's weight (in light clothing without shoes) and height will also be recorded at each testing session using standard protocols, in order to determine their body mass index (BMI). BMI will be calculated as weight in kilograms divided by the square of height in metres (weight/height^2^). Age and gender corrected BMI z scores [64] will be used for analysis.

The child's girth will be measured around the waist circumference using the navel as a guide. Two measurements to the nearest 0.1 cm will be taken using a non-stretch dressmaker's tape. If there is more than 0.5 cm variation between the two measurements a third will be taken. In analysis, the average of the two closest measurements will be used [65].

### Covariates

#### Intelligence

The Wechsler Preschool and Primary Scale of Intelligence (WPPSI-III [66] will be used to examine the children's performance and verbal intelligence. The WPPSI-III is a standardised test measuring intelligence in children between the ages of 3 and 7 years. For the purposes of this study only four sub-scales of the WPPSI will be used. Performance IQ will be determined using the scaled scores of the block design and object assembly subscales. Verbal IQ will be determined using the scales scores of the receptive vocabulary and information subscales. The WPPSI-III has been chosen because it is considered one of the most popular tests for measuring intelligence in children of this age [67]. It was also chosen because the materials are child friendly and scoring has been made easier [66]. The internal consistency ranges from 0.83 to 0.96 [66]. The test retest reliability for verbal IQ is 0.90 and for the performance IQ is 0.84 [66].

#### Sex

It is anticipated that approximately equal numbers of boys and girls will be recruited. However, if this is not the case then sex will be used as a covariate in the analyses.

### Procedure

Following the schools randomized allocation to a control or intervention condition, teacher training and the collation of parental consent (child assent), a qualified and trained research team will visit each school to conduct the initial testing in Term 2 or 3 of the school year. The testing environment will vary slightly from school to school depending on space availability and whilst some testing areas may not be ideal in terms of lack of distraction and privacy, it was considered important for children of this young age to be kept in a familiar environment. Children will be assessed using all of the measures and researchers will monitor levels of interest and fatigue. Children will be provided with incentive stickers or stamps upon the conclusion of each measure.

Parent packs will be sent home with each child containing the Parent SSRS and SDQ Questionnaires together with a general demographic data form. These packs will be returned in sealed envelopes to the Research Coordinator via the class teacher. Teacher packs containing the Teacher SSRS and SDQ will also be provided to each class teacher and teaching relief will be provided to allow for the timely completion of these questionnaires.

Follow up testing will be conducted under similar circumstances 6 months later in Term 4 of the school year, and in Term 3 of the following year when the children have progressed into Year 1. The children will be assessed on all measures again except for the WPPSI-III, and parents and teachers will again complete the SSRS and SDQ forms.

Parents will be given the option of receiving a summary report on the findings of the initial testing and, if appropriately notated on the parent consent form, a similar report will be provided to the schools. In order to maintain confidentiality, parent reports will not contain any of the information provided by teachers in their SSRS or SDQ Questionnaires.

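### Baseline testing and teacher ratings come after allocation and after intervention teachers are trained, so the pre-intervention reference may already differ by arm

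*Protocol article*

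**What the plan says.** Under Intervention and control condition, the article states: "Participating schools will be randomly assigned using a toss of a coin to the control or intervention condition". The toss is made within matched pairs: "Schools will be paired on SES ranking, location and size, with one of the pair being randomly allocated as a control school". Training goes to one arm only: "Teachers from the Intervention schools will be provided with comprehensive training". It covers not just the "activities but on the background and rationale for the project".

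Under Procedure, the sentence that begins "Following the schools randomized allocation to a control or intervention condition, teacher training and the collation of parental consent (child assent" goes on to say that, after these steps, "a qualified and trained research team will visit each school to conduct the initial testing in Term 2 or 3 of the school year". The baseline questionnaires belong to the same stage. Parents receive the SSRS and SDQ through packs sent home, and "Teacher packs containing the Teacher SSRS and SDQ will also be provided to each class teacher".

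Under Analysis, efficacy is judged by the group × time interaction, and all three hypotheses use the pre-intervention score as the reference.

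**The concern.** Randomising schools protects against differences that exist before allocation. It does not protect against differences that arise afterwards. Here the baseline is taken after the arm is known to the intervention teachers, and after the first step of the intervention has been delivered to them.

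Three routes to an arm difference at baseline follow:

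- Intervention teachers rate the children knowing their arm and the expected benefits. This affects the teacher SSRS and SDQ, and so Hypotheses 2 and 3. The pilot's significant result was on the teacher-rated SSRS.
- Trained teachers could use some activities before testing, so that the baseline already contains part of the effect.
- If parents are asked for consent once the arm is known, the consenting children could differ between arms.

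An analysis cannot recover a baseline that was not taken before exposure. The IQ covariate does not help, because it too is measured at this post-allocation visit.

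**Working it through.** **1. The plan's own figures.** The Participants section gives 12 schools with at least 50 children each and 10% non-participation: 12 × 50 × 0.90 = 540, or 270 per arm, as stated. With 30% attrition, 540 × 0.70 = 378, stated as 380. Equal participation in both arms is therefore assumed. No number is in dispute; the point is the sequence.

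**2. What the text fixes and what it leaves open.**

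- Testing after allocation and after training: stated.
- Intervention teachers know their arm at baseline: follows from training them alone.
- Control teachers and parents know the arm: not stated, and nothing described conceals it.
- Consent after allocation: suggested by the order of the list. The sentence strictly says only that allocation, training and consent all precede testing.
- Programme use before baseline: neither stated nor excluded.

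Figure 1 (trial flow) is not available here and might settle the open items.

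**3. How a rating shift enters the test.** Let δ be the true effect on change, b the shift in the intervention arm's baseline ratings, and f the shift in its follow-up ratings. The contrast in change is δ + f − b.

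- If f = b (the same teacher with a stable shift), it cancels.
- If f = 0, the bias is −b. This could apply in Year 1 if an untrained teacher then does the rating; the article does not say who rates in Year 1.
- Taking baseline before allocation and training sets b = 0. It leaves f.

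**4. Early programme use.** If a share e of δ has accrued by baseline, the contrast is (1 − e)δ, a bias toward the null. The document gives no value for e. In the pilot, motor improvement was neither expected nor found after delivery in Terms 2 and 3, so a sizeable motor gain before baseline is unlikely.

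**5. Arm-dependent consent (assumed values).** With non-participation q₁ and q₀ in the two arms, and non-participants lower than participants by D, the baseline level difference is D(q₀ − q₁). Take q₁ = 10%, q₀ = 15% to 30%, and D = 0.3 to 0.8 SD. The range runs from 0.3 × 0.05 = 0.015 SD to 0.8 × 0.20 = 0.16 SD. If that difference is the same at every visit, it contributes nothing to the change contrast. It biases the result only if the missing children would also have changed at a different rate.

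**6. A baseline-only rating shift (illustration, f = 0, δ = 0).** This is a school-level t test with 6 + 6 schools, 30 children per school, 10 df and two-sided 0.05, with the analysed score scaled to SD 1. SE = √{2[ICC + (1 − ICC)/30]/6}, which is 0.120 at ICC 0.01 and 0.165 at ICC 0.05. The chance of a false significant result in the direction the shift produces (nominal 2.5%) is:

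| Shift in baseline (SD) | ICC 0.01 | ICC 0.05 |
|---|---|---|
| 0.1 | 12% | 8% |
| 0.2 | 33% | 19% |
| 0.3 | 62% | 38% |

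The shifts and ICCs are assumptions; the document gives neither. The table does not apply where the shift persists to follow-up.

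**The case against.** A reader might infer that parents decide on participation knowing the arm. The text does not establish this: the order of allocation and consent is not fixed, collating consent may mean gathering in forms, and no section says parents are told the arm. Nor do schools choose to take part knowing their arm, since it is participating schools that are randomised. The programme is delivered to whole classes, and the 10% non-participation is described as relating to testing. Refusing may therefore mean refusing assessment rather than losing the programme, which weakens any incentive to consent differently. These points stand, and the consent strand is a possibility only.

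A reader might also infer that the baseline is already contaminated by programme use. The article calls the first scores pre-intervention, and provides for weekly dosage reports and monitoring visits. An instruction to start only after testing could sit in the fuller protocol. This stands as far as it goes: early use is possible, not shown.

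The strongest objection concerns the ratings. If training changes how teachers rate, training before baseline may put the same shift into both the baseline and the Term 4 ratings, where it cancels. Training after baseline would leave the shift at follow-up only. This stands in part. Resequencing alone does not make the teacher-rated comparison unbiased. But cancellation requires the shift to be equal at both visits, which the present order cannot guarantee and which is least secure in Year 1. The new order makes the baseline comparable between arms and also closes the consent and early-use routes.

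**Conclusion.** The point holds in a limited form. It is explicit that baseline child testing follows allocation and the training of intervention teachers, and the questionnaires belong to that same stage. Intervention teachers therefore rate at baseline knowing their arm, and the reference for the group × time test may already differ by arm. Early programme use and arm-dependent consent are possible but not stated.

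The size cannot be derived from the document. The 0.015 to 0.16 SD range and the false-positive table rest on assumed inputs and are not estimates of bias in this trial. A stable level difference would largely cancel in the change comparison, and early motor exposure would understate the effect rather than create one. The exposure is greatest for the teacher-rated SSRS and SDQ. For the directly tested motor measures it depends also on whether testers know the arm, on which the article is silent. This is a cheap improvement, not a defect that invalidates the design.

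**What to change.** Reorder the Procedure by pair. In both schools of a pair, first complete consent, child testing, and the parent and teacher baseline forms. Then toss the coin for that pair, or disclose a result already drawn. Only then train the intervention teachers and hand over programme materials. State in the text that consent precedes disclosure.

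If allocation has to come first, use staff unaware of it for consent and testing, and report consent rates and baseline scores by arm.

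The change needs no new measures. Its cost is time: training can no longer overlap with baseline. Baseline must be scheduled early enough to keep the programme's stated minimum of 10 weeks before Term 4 post-testing, and a Term 3 baseline leaves the least room. The change does not remove rater awareness at follow-up, which should be acknowledged when the SSRS and SDQ results are interpreted.

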### Trial Flow

Figure 1 provides an overview of the trial flow.

**Figure 1 F1:**
[figure not shown]
**Methods chart**.

### Analysis

This is a multivariate nested cohort design [51]. Schools will be randomly allocated to either the intervention or control condition and students will then be followed as a cohort over time to assess the effects of the intervention on a range of dependent variables. The outcomes for individuals can not be assumed to be independent and will be analysed as a Nested Analyses of Covariance (with covariates of sex and IQ) to assess the efficacy of the intervention program (2 groups × 3 testing times). This will be determined by a significant group x time interaction:

• *Hypothesis 1: *The *Animal Fun *program will result in a significantly greater improvement in fine and gross motor scores (measured by MABC-2 and BOT-2) compared with controls when comparing the pre-intervention score with post- intervention score in Pre-Primary and at 1 year follow-up.

• *Hypothesis 2*: The *Animal Fun *program will result in a significantly greater improvement in social skills (measured by SSRS) and perceived competence (measured by PSPCSA) compared with controls when comparing the pre- intervention score with post- intervention scores and at 1 year follow-up.

• *Hypothesis 3*: The Animal Fun program will result in a significantly greater improvement in behavioural problems (measured by SDQ and SSRS) compared with controls when comparing the pre- intervention score with the post- intervention scores and at 1 year follow-up score.

• BMI and girth measurements: These variables will be exploratory.

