## Methods/Design

### Design and Aims

This study will use a randomized, cluster controlled trial to examine the influence of a school-based movement and psychosocial program on the physical and mental health of young children in their first years of school. A multivariate nested cohort design [51] will be used to examine the physical (motor coordination; BMI) and psychosocial (self perceptions, anxiety, social competence) outcomes of the program at the end of the Pre-Primary year and also 1 year later after the transition to primary school. Pre-intervention scores on motor and psychosocial variables for both control and intervention schools will be compared with post-intervention scores and scores taken 12 months later in Year 1.

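### Efficacy is judged on change from baseline, adjusted for sex and IQ but not for the child's own baseline score, which costs some precision but not validity

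*Protocol article*

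**What the plan says.** The Analysis section of the protocol article states that outcomes "will be analysed as a Nested Analyses of Covariance (with covariates of sex and IQ) to assess the efficacy of the intervention program (2 groups" by 3 testing times). On success it says: "This will be determined by a significant group x time interaction". Hypothesis 1 expects greater improvement in the intervention arm "when comparing the pre-intervention score with post- intervention score in Pre-Primary and at 1 year follow-up", and Hypotheses 2 and 3 are framed the same way.

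The three occasions are pre-intervention, the end of Pre-Primary and Year 1. Design and Aims describes the comparison likewise: "Pre-intervention scores on motor and psychosocial variables for both control and intervention schools will be compared with post-intervention scores and scores taken 12 months later".

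The Covariates section lists only intelligence and sex. On sex it expects about equal numbers of boys and girls and adds: "However, if this is not the case then sex will be used as a covariate in the analyses". The child's own pre-intervention score is nowhere named as a covariate, although it is available for every outcome in the three hypotheses. The Procedure section says of follow-up: "The children will be assessed on all measures again except for the WPPSI-III, and parents and teachers will again complete the SSRS and SDQ forms".

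**The concern.** Because the pre-test is one of the three levels of time, an interaction contrast between pre-test and a follow-up is the difference between arms in mean change. A change score fixes the slope of follow-up on baseline at 1. When the correlation between occasions is below 1 and the SDs are similar, the best slope is smaller, so the change score carries more baseline noise than it needs to.

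Sex and IQ do not replace the baseline score: neither is the child's starting level on the outcome. The choice of contrast does not avoid the loss either. The 2-df interaction is jointly a test of the two change differences, and a single 1-df contrast from the same model has the same variance.

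At stake is precision for all three hypotheses in a trial with only 12 schools. The measurement that would sharpen the comparison is already being collected. The model, its covariates and the success criterion are all stated, so this is a choice made in the text rather than detail left to another document.

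**Working it through.** **The plan's own figure.** The Participants section says that about 15 children per school in 12 schools gives 80% power for the movement variables: 15 × 12 = 180. It expects 540 children at first testing and 30% loss: 540 × 0.70 = 378, against 380 stated, which agrees after rounding. Retained children per school are 380/12 = 31.7. The 80% itself cannot be reproduced, because effect size, SD, ICC, alpha and pre-post correlation are not given.

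**Inputs for rho.** The article gives only test-retest reliabilities: MABC at least 0.75 (original version), BOT-2 0.87 (complete battery; the trial uses the Short Form), PSPCSA .62 to .81 over 10 to 22 days, and SDQ total difficulties .96 over 2 weeks. The trial's intervals are about 6 months and then into the following school year, so these are plausible upper bounds. A rho of 0.5 is my assumption for a less stable measure.

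**Variance.** Take SD 1 at both occasions.
- Change score: 2(1 − rho).
- Baseline as covariate: 1 − rho².
- Ratio, adjusted to change: (1 + rho)/2.

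**Power.** Assume two-sided alpha 0.05 and a t test on 10 df (12 schools, pairing ignored). The critical value is 2.228, and 80% power needs a noncentrality of 3.110. Adjustment divides this by √((1 + rho)/2).

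| rho | change variance | adjusted variance | ratio | power, change | power, adjusted | cut in detectable effect |
|---|---|---|---|---|---|---|
| 0.5 | 1.00 | 0.75 | 0.75 | 80% | 90% | 13% |
| 0.6 | 0.80 | 0.64 | 0.80 | 80% | 88% | 11% |
| 0.75 | 0.50 | 0.4375 | 0.875 | 80% | 85% | 6% |
| 0.87 | 0.26 | 0.243 | 0.935 | 80% | 83% | 3% |
| 0.96 | 0.08 | 0.078 | 0.98 | 80% | 81% | 1% |

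**Clustering.** The ratio is unchanged if school-level and child-level correlations are equal. With child-level rho 0.75, school-level rho of 0.5 or 0.9, ICC 0.01 to 0.10 and 15 or 31.7 children per school, it lies between 0.77 and 0.92.

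**Simulation.** 20,000 runs, 6 against 6 schools, 15 children each, ICC 0.05. Power, change against adjusted:
- rho 0.5, effect 0.55 SD: 72% against 84%.
- rho 0.75, effect 0.40 SD: 75% against 80%.
- rho 0.87, effect 0.29 SD: 75% against 77%.

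Type I error was about 5% for both analyses in every setting.

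**If the claimed cushion is real.** Suppose the change analysis has 80% power at 15 per school. At 31.7 per school the noncentrality is multiplied by √{[(1 + 14·ICC)/15] / [(1 + 30.7·ICC)/31.7]}.
- ICC 0.05: factor 1.190. Planned power is 91%; adjusted 97% at rho 0.5 and 94% at rho 0.75.
- ICC 0.02: factor 1.294. Planned power is 95%; adjusted 99% at rho 0.5 and 97% at rho 0.75.

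The gain is then about 2 to 6 points.

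**Unequal SDs.** If the follow-up SD is k times the baseline SD, the ratio is k²(1 − rho²)/(1 + k² − 2·rho·k). At rho 0.75 it is 0.875 for k = 1, 0.984 for k = 1.2 and 1.00 for k = 1.33. It never exceeds 1, because the difference in variance is (1 − rho·k)².

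**The case against.** The strongest reply is that group by time over three occasions is a recognised analysis, matches hypotheses worded as improvement, and controls type I error. All of that stands. A reader might infer that regression to the mean turns a chance low start into a false effect, so that the planned test is biased. The documents do not support this. Under random allocation a chance imbalance favours either arm equally, so the change contrast is unbiased. In one particular trial a baseline difference d (in SD units, equal SDs) is over-corrected by (1 − rho)d, but the spread this causes is already in the variance ratio and is not a second harm. Schools are also paired on SES ranking, location and size before the coin toss, which should reduce such differences without removing them.

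The gain is modest at the protocol's own motor reliabilities: 3 to 5 points from 80%. It almost vanishes at the SDQ figure of .96, so it would be wrong to name the SDQ as a clear gainer. Teacher ratings in Year 1 may come from a different teacher and agree less with baseline, but no figure supports a size.

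The Participants section says the retained sample is double that needed. If so, less is at stake. The claim cannot be checked, however, and it covers only the movement variables.

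Finally, the Procedure section places collation of consent and initial testing after allocation and teacher training. If consent differed by arm, baseline differences might be real, and adjustment for an error-prone baseline could leave bias. This is a reason to keep the change contrast as a check. It does not make that contrast the better main analysis of a randomised comparison.

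**Conclusion.** The point holds as a loss of precision. The stated model makes each effect a difference in change and leaves the child's own baseline score out of the covariates. With equal SDs this inflates the variance by 2/(1 + rho): 33% at rho 0.5, 14% at 0.75, 7% at 0.87 and 2% at 0.96. From a base of 80% power, the forgone gain is about 10, 5, 3 and 1 points. It is smaller if SDs grow moderately over time, and about 2 to 6 points for the movement variables (rho 0.5 to 0.75, ICC 0.02 to 0.05) if the double-sample claim is taken literally.

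These sizes rest on an assumed rho and ICC, alpha 0.05 and 10 df with pairing ignored. A reader might go further and call the planned test invalid, or the trial underpowered because of it. Neither follows: type I error is kept, and the power the trial actually has cannot be derived from the article.

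**What to change.** In the Analysis section, take the Term 4 and Year 1 scores as outcomes (2 groups × 2 follow-up times), with school as a random cluster and repeated scores linked within child. Add the child's pre-intervention score on the same measure and its interaction with time as covariates beside sex and IQ. An equivalent route keeps all three times and constrains the arm means to be equal at baseline. Read the effect as the adjusted group difference at each follow-up, and reword the interaction criterion to match.

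Keep the unadjusted change contrast as a sensitivity analysis, because consent and initial testing follow allocation.

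The cost is wording and a simple, pre-stated rule for children without a baseline score, which a change score needs as well. No further data or children are required.
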